##### Secondary outcome — walking capacity

The 6-min walk test (6MWT) will be used to measure walking capacity. Participants will walk along a 20-m straight course as many times as possible within 6 min [79]. The primary outcome of this test is the distance walked (in meters) during the test. Pre and post-test resting BP, HR, and RPE will also be assessed. During this test, participants will be permitted to use gait aids.

##### Secondary outcome — motor learning

For this study, we will use a computerized visuomotor task that will require modulating force [22] during a hand-grasping, as this skill is essential in the performance of many activities of daily living. The participant will be seated in front of a computer screen and be asked to make a fist applying force with their most affected hand on a handgrip. If the affected hand is unable to hold or modulate force on the handgrip due to disability, the unaffected side will be used.

This handgrip will control the position of the cursor displayed on the screen. The goal of the motor task will be to apply appropriate force in order to move the cursor so that it touches as many targets on the screen, as accurately as possible. Participants will perform 4 blocks of 20 trials, and the score for each block will be calculated as the total time that the cursor is on the target areas, divided by the total time of each trial, multiplied by 100.

#### Psychosocial responses to exercise

##### Secondary outcome — enjoyment

Enjoyment will be assessed after week 6 and T1, using the Physical Activity Enjoyment Scale (PACES), which has been validated for older adults with functional limitations [80] and people with multiple sclerosis [81]. Participants will be asked to respond to the prompt, “Please rate how you feel at this moment about the exercise you have been doing” in relation to several domains using a 7-point scale (e.g., 1=does not make me happy, 7=makes me happy). A total score is calculated (ranging from 8 to 56). Higher scores indicate greater enjoyment.

##### Secondary outcome — motivation

The Behavioral Regulation Exercise Questionnaire-3 [80, 82] will be used to assess participants’ motivation for physical activity at T0, T1, and T2 and will be administered after the 1st week of training and at the end of training. Participants will respond to 24 items using a 5-point Likert scale (e.g., 0=not true for me, 4=very true for me), covering different types of motivations. Autonomous motivation (i.e., internally regulated motivation) scores will be calculated by averaging the score on the identified, integrated, and intrinsic regulation subscales. External motivation will consist of the mean of the external and introjected regulation scores. Earlier versions of this questionnaire (BREQ-2) have been described as reliable and have been validated questionnaire previously in individuals with coronary heart disease [83, 84]

For both questionnaires, French or English versions will be provided depending on the language preference of the participant. If a participant has a speech or language difficulty, assessors will utilize a third party to provide clarification of the questionnaire items and participant responses.

### Sample size estimation

Based on previous data [21] and using a linear mixed model, we estimated that we would require 32 participants per group (*n* = 64 total) to detect a 5% increase at T1 in the resting MEP amplitude and intracortical inhibition of the affected hemisphere’s M1 in the HIIT group. An increase of 5% is associated with improved motor function in stroke [2]; therefore, we will consider this difference between HIIT and MICT groups to be clinically significant. The statistical package G*Power was used to determine the sample size required to obtain a power of 80% (alpha < 0.05). We have increased the sample size to 40 per group (*n*=80 total) to accommodate for a 20% attrition rate.

### Statistical analysis

Estimates of the effect of HIIT and MICT at the end of the intervention (T1) for all outcomes will be determined using linear mixed models. Baseline scores (at T0), age, and sex will be included as covariates for sub-analysis. The primary analysis focuses on T1, but T2 will also be included in the model (except for enjoyment, which will not be measured at T2) to increase the statistical efficiency of the estimate. If group interaction effects are significant, *t*-tests based on the linear mixed models will be employed as planned pairwise comparisons to determine differences between HIIT and MICT. Sex-based subgroup analyses will also be performed for exploratory purposes.

Participant data will be analyzed based on intention-to-treat; therefore, linear mixed models will be the preferred method of analysis as it is more flexible than the analysis of variance, and allows for the correlation of repeated measures within subjects and missing data, as long as missing data are missing at random [85]. Interactions between changes between primary and secondary outcomes will be explored with the Freedman-Schatzkin test, which allows for the identification of mediators of change in small-scale exercise studies [86].

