## Outcomes

### Assessments

Prior to the initial assessment, the assessor will obtain written consent from the participant. Baseline descriptive characteristics will be collected at T0 and include biological sex, age, weight, height, body mass index, education level, characteristics of stroke, and past medical history. Additionally, the degree of neurological deficit (National Institutes of Health Stroke Scale, NIHSS [60]), upper limb motor function (Chedoke McMaster Stroke Assessment, CMSA [61]), and global cognitive function (Montreal Cognitive Assessment [62]) will be assessed at baseline. Medication use will be recorded at all time points. PASIPD [59] will be assessed at all time points and midway through the 8-week follow-up (week 16), to account for changes in physical activity between T1 and T2. All outcomes, apart from enjoyment, will be collected T0–T2 at both sites. To minimize participant fatigue, assessments will take place over 3 days (1.5 h each). Data collection forms can be provided by study PIs upon request. Figure 3 provides a timeline and collection of outcomes.

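### Adjustment for the T0 score is reserved for a sub-analysis; the primary T1 contrast is valid but likely less precise than it could be at no cost

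*Protocol article*

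**What the plan says.** All of the following is in the protocol article.

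- **Statistical analysis**, on covariates: "Baseline scores (at T0), age, and sex will be included as covariates for sub-analysis". No covariate is assigned to the primary model.
- **Statistical analysis**, on the primary contrast: "The primary analysis focuses on T1, but T2 will also be included in the model". The reason given for adding T2 is efficiency. The section does not say whether T0 enters as a repeated response.
- **Statistical analysis**, on the test sequence: model-based t-tests of HIIT against MICT follow "If group interaction effects are significant".
- **Assessments**: "All outcomes, apart from enjoyment, will be collected T0–T2 at both sites". A T0 value is therefore planned for every outcome except enjoyment. Under **Randomization**, allocation is revealed only after T0 is complete, and site is the only stratification factor.
- **Sample size estimation**: "we estimated that we would require 32 participants per group", for a power of 80% at alpha 0.05, "to detect a 5% increase at T1 in the resting MEP amplitude and intracortical inhibition". Neither a standard deviation nor a T0–T1 correlation is given.

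**The concern.** A pre-randomization measurement of the outcome is usually informative about its later value, and adjusting for it removes the part of the T1 variance that it explains. The article moves that adjustment out of the primary analysis while seeking efficiency from T2. With complete data, separate group means at each visit and an unstructured covariance, T2 adds nothing to the T1 contrast; it helps only where T1 values are missing. T0 is the measurement that could supply the precision sought.

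At stake is the precision of the primary estimate with about 32 evaluable participants per group. Randomization does not balance baseline excitability beyond chance, and an unadjusted contrast carries any chance imbalance as extra noise.

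**Working it through.** **Inputs from the article:** 32 evaluable per group, 1:1 allocation, 80% power, alpha 0.05, 20% attrition. **Assumptions:** two-sided test (sidedness is not stated), complete data, equal variance at T0 and T1, and r = 0.3, 0.5 or 0.7.

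**1. The plan's own figure.** The attrition step reproduces: 32/0.8 = 40 per group and 64/0.8 = 80 in total. The 32 itself cannot be reproduced without a standard deviation. Solving backwards with the normal approximation, the standardized difference is (1.960 + 0.842) × √(2/32) = 0.70. With the t distribution it is 0.71.

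**2. Relative variance of the T1 group contrast**, by the role given to T0 (checked by generalized least squares):

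- T0 not in the model (T1 and T2 only): 1.
- T0 a response with separate group means: still 1 for the pairwise contrast at T1, and 2(1−r) for the group-by-time contrast T1 minus T0.
- T0 a covariate, or a response with a common mean across arms: 1−r².

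The change contrast exceeds the adjusted one by 2(1−r) − (1−r²) = (1−r)², which is positive for every r below 1. The raw contrast exceeds it by r², which is positive for every r other than 0.

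| r | Raw T1 | Change, 2(1−r) | Adjusted, 1−r² | Raw ÷ adjusted | Change ÷ adjusted |
|---|---|---|---|---|---|
| 0.3 | 1 | 1.40 | 0.91 | 1.10 | 1.54 |
| 0.5 | 1 | 1.00 | 0.75 | 1.33 | 1.33 |
| 0.7 | 1 | 0.60 | 0.51 | 1.96 | 1.18 |

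**3. Power if 32 per group gives 80% for the raw T1 contrast.** The expected test statistic is 2.802 unadjusted and 2.802/√(1−r²) adjusted. Power is Φ(expected statistic − 1.960). For the change contrast, the divisor is √(2(1−r)).

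| r | Raw | Change | Adjusted | Per group for 80% if adjusted |
|---|---|---|---|---|
| 0.3 | 80% | 65.8% | 83.6% | 30 |
| 0.5 | 80% | 80.0% | 89.9% | 24 |
| 0.7 | 80% | 95.1% | 97.5% | 17 |

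**4. Power if 32 per group was sized on the adjusted variance and T0 is then left out.** The expected statistic becomes 2.802 × √(1−r²):

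- r = 0.3: 2.673, power 76.2%.
- r = 0.5: 2.426, power 68.0%.
- r = 0.7: 2.001, power 51.6%.

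Steps 3 and 4 are alternatives, and the article does not say which of them describes its calculation.

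**The case against.** The strongest reply is that the primary model may already use T0. The reference to a group interaction, the talk of repeated measures and the objective of assessing change all fit a group-by-time model over T0, T1 and T2. If that model has a common T0 mean across arms, it matches adjustment and nothing is lost. This stands in part: a reader might infer that the plan throws T0 away, and the text does not establish that. It does not state the common-mean model either. With separate group means at T0, the group-by-time contrast is less precise than the adjusted one, and the follow-up comparison at T1 is still a raw difference.

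Four further limits are accepted.

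- **Size.** It rests on an assumed r. At 0.3, adjustment gains under 4 percentage points of power over a raw T1 contrast. Nothing in the article shows that T0 is the strongest predictor.
- **Power shortfall.** The 76% to 52% figures might be read as showing an underpowered trial. They hold only if 32 was sized on the adjusted variance, which the sample size section does not say.
- **Bias.** Chance imbalance might be read as bias. Under randomization it is part of the sampling error that an unadjusted interval already covers.
- **Which result decides.** The adjusted and unadjusted results might be thought to compete. The article names one analysis primary and places the covariates in a sub-analysis, so the order is clear.

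A statistical analysis plan could supply details such as the covariance structure. The role of the baseline covariate, however, is something the article does fix.

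**Conclusion.** The point holds as one of efficiency. The article places adjustment for T0 outside the primary analysis. Under each reading except a common-mean model that it does not state, the T1 comparison is less precise than one using data already planned for collection. The direction is certain for any r between 0 and 1. Over r = 0.3 to 0.7, the variance penalty is 1.10 to 1.96 times for a raw contrast and 1.54 to 1.18 times for change from baseline. The primary comparison remains valid, and failure to reach the stated 80% power is not shown. This is a free improvement to the plan, not the repair of an invalid analysis. It does not apply to enjoyment, which has no T0 score.

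**What to change.** State the baseline-adjusted model as primary, in one of two equivalent forms:

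- T1 and T2 as responses, with fixed effects for group, visit, group by visit, T0 value, T0 by visit and site (the stratification factor), and an unstructured within-participant covariance; or
- T0, T1 and T2 as responses, with a common T0 mean across arms, and site included.

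Say explicitly that T0 is never both a response and a covariate in the same model. Age and sex may stay in the sub-analysis. Give enjoyment, measured only at week 6 and T1, its own model with no T0 term and no T2 response.

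The cost is wording only: no added visits, measurements or participants. The change should be made and dated before allocation is unblinded for analysis. It would also help to state which variance and which T0–T1 correlation lie behind the 32 per group.

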### Hypotheses

We hypothesize that HIIT will be more effective in promoting neuroplasticity. HIIT will increase the excitability of upper limb representational areas on M1 of the lesioned hemisphere. This will lead to a reduction in the imbalances in M1 excitability that is typically observed in chronic stroke [43, 44]. Based on previous findings [22], we will also expect that the increases in M1 excitability in the lesioned hemisphere after HIIT will be partially mediated by a reduction in intracortical inhibition [45], which is a marker that has been described to increase post-stroke, negatively affecting recovery [8]. HIIT is also expected to be more effective in improving cardiovascular measures of resting BP, arterial stiffness, and VO_2_peak [32, 35]. We predict that after a period of 8 weeks post-termination of the training program (T2), these improvements in neuroplasticity and cardiovascular health will be maintained after to a greater extent in the HIIT group, in comparison to the participants in the MICT group.

We also anticipate greater improvement in walking speed [46], and motor learning post-HIIT, due to an increase in neuromuscular recruitment due to high-intensity exercise, and the aforementioned changes in neuroplasticity, respectively [22]. In contrast, we will also expect a similar improvement in walking capacity in response to either HIIT or MICT. Additionally, responses of motivation and enjoyment will be similar in both groups.

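### The HIIT-versus-MICT test at T1 is conditional on an unnamed group interaction; a single planned contrast needs no such gate, and the gate costs power

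*Protocol article*

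**What the plan says.** Under Statistical analysis, the protocol article opens with an unconditional plan: "Estimates of the effect of HIIT and MICT at the end of the intervention (T1) for all outcomes" come from linear mixed models. It then sets the time points: "The primary analysis focuses on T1, but T2 will also be included in the model", with enjoyment excepted and statistical efficiency given as the reason. On baseline it says "Baseline scores (at T0), age, and sex will be included as covariates for sub-analysis".

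The testing rule comes next. "If group interaction effects are significant", t-tests based on the mixed models "will be employed as planned pairwise comparisons to determine differences between HIIT and MICT". The interaction is not specified further.

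Two other sections bear on this. Sample size estimation sizes the trial "to detect a 5% increase at T1 in the resting MEP amplitude" and intracortical inhibition in the HIIT group, treats that 5% as the HIIT–MICT difference of interest, and gives 32 per group for 80% power at alpha 0.05, raised to 40 for 20% attrition. Hypotheses predicts that at T2 "these improvements in neuroplasticity and cardiovascular health will be maintained after to a greater extent in the HIIT group" than in the MICT group.

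**The concern.** The primary question is one contrast: HIIT minus MICT at T1. The only between-arm test that the article describes for it is placed behind a different question, namely whether some group interaction is significant.

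The gate is not needed to control the error rate of that contrast, because a single pre-specified test at 5% is already a 5% test. When the effect is real, a two-step rule cannot reject more often than its second step alone, and it will generally reject less often. T2 is brought in to sharpen the T1 estimate, yet under the gate the T2 data can stop the T1 test from being run.

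At stake is the power of the primary test. How much is lost depends on which interaction is meant and which visits are responses, and the article fixes neither.

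**Working it through.** **Inputs from the article.** 32 per group before attrition, 1:1 allocation, 80% power, alpha 0.05, 5% difference at T1.

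**Assumed.** Two-sided test; equal correlation ρ between visits of 0.3, 0.5 or 0.7; equal variances; complete data on 32 per group. The article gives no SD, correlation or G*Power test family.

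**The plan's own figures.** Attrition: 32 / (1 − 0.20) = 40 per group, which agrees with the article. The 32 itself cannot be reproduced without an SD. Solving backwards with the two-sample t-test on 62 df, 80% power requires a standardised difference d = 0.711 (noncentrality d × √(n/2) = 0.711 × √16 = 2.84). For a 5% effect that implies an SD of 5 / 0.711 ≈ 7.0 percentage points. This only restates the 80%; it does not confirm it.

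**What the gate tests.** Let the arm difference be Δ at T1 and fΔ at T2, with none at T0 because of randomisation.

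- *Model A: T0, T1 and T2 are responses.* Group-by-time is a 2-df test of the pair (Δ, fΔ). A sustained effect (f = 1) gives (Δ, Δ), which is not zero, so the gate can open.
- *Model B: T0 is a covariate; T1 and T2 are responses.* Group-by-time is a 1-df test of Δ − fΔ = (1 − f)Δ. With f = 1 this is exactly zero, so the gate opens only at its 5% false-positive rate.

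**Setting the effect.** Δ is chosen so that the ungated T1 test has 80% power. In units of the single-visit SD:

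- change from baseline: Δ = 0.711 × √(2(1 − ρ)), which is 0.711 at ρ = 0.5 and 0.551 at ρ = 0.7;
- baseline-adjusted (ANCOVA): Δ = 0.711 × √(1 − ρ²), which is 0.616 at ρ = 0.5 and 0.508 at ρ = 0.7.

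**Simulated power of gate plus T1 test** (20,000 trials per scenario; ranges cover ρ from 0.3 to 0.7; ungated power 80% in every row):

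| Gate and T1 test | Effect sustained (f = 1) | Half lost by T2 (f = 0.5) |
|---|---|---|
| A, change from baseline | 75–76% | 68–70% |
| A, baseline-adjusted T1 test (random-intercept gate) | 58–69% | 49–62% |
| B, baseline-adjusted T1 test | about 3% | 20–24% |

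In the first row the gate opens in about 82–84% of trials when the effect is sustained. In the last row it opens in about 5%. If the effect has gone entirely by T2 (f = 0), model B recovers to about 57–64%, and model A with the change test stays near 75–76%.

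**After the fix.** With no gate, the T1 contrast has 80% power by construction. The sample size does not change.

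**The case against.** A reader might infer that the arms may never be compared, or that the trial's power is essentially gone. The documents do not support that, for these reasons:

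- **Estimates are not gated.** The T1 effect estimates are planned for all outcomes without condition. Only the t-tests wait on the interaction.
- **The near-total loss belongs to model B, the less natural reading.** Baseline as a covariate is mentioned only for sub-analysis, which points to T0 being a response in the main model.
- **Even in model B a sustained benefit need not go undetected.** The group term averaged over T1 and T2 is not gated. With a fully sustained effect and ungated T1 power of 80%, it is significant in about 91–95% of simulated trials. That average is not the T1 contrast, however.
- **The hypothesis is not an equal effect at T1 and T2.** It predicts better maintenance with HIIT. If MICT loses more, the difference grows after T1 and an interaction exists.
- **A gate also removes false positives.** The rule follows a sentence covering all outcomes, where an omnibus step has a recognisable purpose.
- **The 80% may not belong to the T1 contrast.** If G*Power was run for an interaction, the gate is what was powered.

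All of this stands, and it limits the size of the problem. It does not justify the gate for the one primary contrast. Nor can the point be set aside as detail left to a fuller document: the article states a decision rule, and the rule is a poor one for its primary question.

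**Conclusion.** The concern holds in a limited form. The article makes the significance test of its primary comparison conditional on an interaction that it does not name, and no allowance for this is visible in the sample size.

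If the 80% is the power of the T1 contrast and T0, T1 and T2 are all responses, the loss for a change-from-baseline test is about 5 points for a sustained effect and about 10 to 12 points if half is lost by T2. It is larger if the T1 test is baseline-adjusted behind the same gate. The figure of about 3% requires both model B and an equal effect at T1 and T2, and should be quoted only with those conditions.

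The direction of the loss is secure under either model. Its size rests on assumed correlations, complete data and an unstated G*Power calculation. Should-fix, with moderate confidence in the magnitude.

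**What to change.** In the Statistical analysis section:

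1. Delete the condition on the interaction.
2. Name the HIIT minus MICT contrast at T1 from the mixed model as the primary test, two-sided at 5%, reported with its 95% CI whatever the interaction p-value.
3. Report the T2 contrast in the same way as secondary, and the group-by-time interaction descriptively.
4. State whether T0 is a response or a covariate in the main model.

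In Sample size estimation, state which test the 80% refers to, with the SD, correlation and sidedness behind 32 per group.

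The cost is a few sentences, with no new participants or data. The change should be made before group labels are revealed to the analyst; the Blinding section says allocation is masked in data analysis, so that order can be kept.

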### Randomization

The unit of randomization will be the participant. The randomization process will use a computer-generated group assignment (http://www.randomizer.org) with a 1:1 allocation ratio into either HIIT or MICT training groups. Participants will be stratified between both sites (JRH and McMaster), and we will conduct the randomization with a variable block size unknown to each site. PIs MR and AT will conduct and conceal the allocation of their counterpart’s site (MR for McMaster, AT for JRH). Upon obtainment of participant consent and completion of baseline assessments (T0), group allocation will be revealed to the participant and assessor.

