### Secondary outcomes

#### Neuroplasticity

##### Secondary outcome

Short intracortical inhibition and intracortical facilitation (SICI and ICF)

SICI and ICF will be measured using a paired-pulse TMS protocol that will use a conditioning stimulus of 80% RMT, followed by a supra-threshold stimulus (120% RMT) delivered at rest after 2.5ms (inhibition) and 12ms (facilitation), respectively. These intervals between stimuli capture changes in excitability after motor learning [69] and are susceptible to change with exercise in people with chronic stroke [22]. The amplitude of the MEP elicited by the send stimulus normalized to the MEP amplitude at baseline will provide an estimate of inhibition and facilitation [45]. A total of 25 paired pulses (separated by 2s), per hemisphere, will be delivered at the FDI. Our laboratory has used these measures of excitability in a previous study to investigate the effects of a single bout of HIIT in individuals with chronic stroke [22]. ICF and SICI are important markers of neuroplasticity, specifically related to motor learning processes [45, 70], and have been used to predict motor recovery post-stroke [8].

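### Used alone, the Freedman-Schatzkin test can declare a mediator on which HIIT and MICT do not differ, far more often than 5% when outcome changes are moderately correlated

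*Protocol article*

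**What the plan says.** The Statistical analysis section of the protocol article states that "Interactions between changes between primary and secondary outcomes will be explored" and names one method for this, the "Freedman-Schatzkin test, which allows for the identification of mediators of change in small-scale exercise studies". It attaches no further condition, such as a difference between the arms on the candidate mediator.

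The Hypotheses section supplies a specific mediation claim: that "increases in M1 excitability in the lesioned hemisphere after HIIT will be partially mediated by a reduction in intracortical inhibition". Inhibition is measured as short intracortical inhibition (SICI), a conditioned motor-evoked potential (MEP) amplitude "normalized to the MEP amplitude at baseline will provide an estimate of inhibition and facilitation". The primary outcome is MEP amplitude.

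On size, the Sample size estimation section says "we estimated that we would require 32 participants per group", 64 in total, raised to 80 for 20% attrition. Participants are allocated "with a 1:1 allocation ratio into either HIIT or MICT training groups". The article gives no correlation between changes in outcomes and no error rate for the mediation test.

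**The concern.** Mediation of a HIIT-MICT difference needs two links: the arms must differ on the mediator (path a), and the mediator must relate to the outcome within arm (path b). The null is that the product ab is zero, which includes the case a = 0. A test that ignores the uncertainty in a protects against b = 0 but not against a = 0.

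Changes in related physiological measures on the same people will often be correlated, so b is often non-zero. The trial could then report that HIIT works through reduced inhibition, or through another secondary outcome, when the two programmes changed that mediator equally.

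**Working it through.** **Inputs from the article.** 64 analysable and 80 randomised (Sample size estimation); 1:1 allocation (Randomization); alpha 0.05, taken as two-sided because the article does not say. The attrition step reproduces: 32/0.8 = 40 per group and 64/0.8 = 80 in total. The 32 per group cannot be rebuilt, as no SD is given; back-solving a two-sided t-test at 80% power gives a standardised difference of about 0.71.

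**Assumed inputs.** The within-arm correlation (rho) between change in mediator and change in outcome, varied from 0 to 0.8; normal changes with unit variance.

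**The test.** The article prints no formula. The standard form compares the arm coefficient without the mediator (tau) and with it (tau'):

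t = (tau - tau') / sqrt(s_tau^2 + s_tau'^2 - 2 s_tau s_tau' sqrt(1 - r^2)), on N - 2 df, where r is the arm-mediator correlation.

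**What the standard error leaves out.** Write Sxx for the arm sum of squares.

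- By least-squares identity, tau - tau' = a_hat × b_hat.
- The factor sqrt(1 - r^2) is the correlation of the two arm coefficients when arm and mediator are held fixed.
- With residual SDs s1 (without the mediator) and s2 (with it), s_tau = s1/sqrt(Sxx) and s_tau' = s2/sqrt(Sxx(1 - r^2)).
- The squared denominator is then [(s1 - s2)^2 + s2^2 r^2/(1 - r^2)] / Sxx.
- The second term equals a_hat^2 times the variance of b_hat. No term carries the variance of a_hat.
- If s1 = s2, a_hat cancels and t is, apart from sign, the ordinary t statistic for b. The first term, which grows with rho, is what keeps the rejection rate below 100%.

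**Hand check at a = 0, rho = 0.5, N = 64.** Put a_hat = z/sqrt(Sxx) with z standard normal. Then s1 = 1, s2 = sqrt(0.75) = 0.866 and r^2 is about z^2/64. Rejection needs 0.25 z^2 > 4 × [(1 - 0.866)^2 + 0.75 z^2/64] = 0.072 + 0.047 z^2. So z^2 > 0.072/0.203 = 0.354, that is |z| > 0.595, which has probability about 0.55.

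**Simulation.** 40,000 replicates per cell, no arm difference on the mediator, percentage declared a mediator at two-sided 0.05. Joint significance means that paths a and b are both significant.

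| rho | Freedman-Schatzkin, N = 64 | N = 80 | Joint significance, N = 64 | N = 80 |
|---|---|---|---|---|
| 0 | 2.9 | 3.1 | 0.3 | 0.3 |
| 0.1 | 7.0 | 8.9 | 0.6 | 0.6 |
| 0.15 | 12.9 | 16.7 | 1.0 | 1.2 |
| 0.2 | 21.2 | 27.8 | 1.7 | 2.0 |
| 0.3 | 41.8 | 50.8 | 3.2 | 3.8 |
| 0.4 | 55.1 | 60.8 | 4.5 | 4.6 |
| 0.5 | 55.9 | 57.7 | 5.0 | 5.1 |
| 0.6 | 49.7 | 50.0 | 5.1 | 5.0 |
| 0.7 | 41.1 | 41.6 | 4.9 | 5.2 |
| 0.8 | 31.9 | 32.1 | 5.0 | 4.8 |

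- A direct arm effect of 0.7 on the outcome moves no Freedman-Schatzkin rate by more than 0.4 points.
- Under the other null (arms differ on the mediator by 0.3 to 0.7 SD, mediator unrelated to outcome) the test keeps its level: 3.8-5.0%.
- A percentile bootstrap of the product, at a = 0, rho = 0.5 and N = 64, rejects in about 6% (2,000 replicates).

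**The case against.** **The arm-to-mediator effect is estimated anyway.** The Statistical analysis section estimates arm effects at T1 for all outcomes, SICI included. If a mediator were claimed only when that contrast was also significant, the false rate would be 0.5-5.2% at N = 64 and 0.7-5.3% at N = 80 (rho 0.1 to 0.7). This is the strongest reply, and it shows that the gap is one missing condition. But the section does not state that condition. Requiring only a significant arm effect on the outcome is not enough: with a real 0.7 SD direct effect and no arm difference on the mediator, the test still declares mediation in 41% (rho 0.3) and 55% (rho 0.5) of the trials that pass.

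**The analysis is exploratory, and the supporting source and any analysis plan are not shown.** The exploratory status stands and limits the consequence. The cited source may recommend safeguards that cannot be checked here. Even so, the article itself fixes the test and credits it with identifying mediators, which goes beyond leaving detail to another document.

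**Stronger readings that the documents do not support.**

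- A reader might infer that the test rejects whenever two changes are correlated. It does not: the rate peaks near 61% and is 7-9% at a correlation of 0.1.
- A reader might infer that the null is no effect of training. Both arms train, so it is no HIIT-MICT difference.
- A reader might infer that SICI and the primary MEP share noise by construction. The article does not say which MEP block normalises SICI. The primary measure averages stimulations at rest and during contraction, while SICI is measured at rest. Shared noise is plausible, but its size is unknown.
- A reader might infer that mediators will often be claimed when the arms differ on neither outcome. The hypothesis presupposes an excitability gain. If a significant outcome contrast is required first, such claims arise in 0.3-4.5% of trials (rho 0.1 to 0.7).

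**Conclusion.** The concern holds for mediation statements only. Applied without a condition on the arm-to-mediator effect, the named test does not control error for the question in the Hypotheses section. With no HIIT-MICT difference on the mediator, the false-mediation rate is about 21-56% at N = 64 and 28-61% at N = 80 for correlations of 0.2 to 0.7. It is close to nominal or below only when the correlation is near zero. These figures rest on the standard form of the test, normal changes, a two-sided 5% level and assumed correlations. The mechanism follows from least-squares algebra; the size in this trial depends on a correlation that the article does not report. The primary T1 comparison, the sample size and the secondary contrasts are untouched.

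**What to change.** In the Statistical analysis section:

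- Declare mediation only if the arm-to-mediator effect and the mediator-to-outcome slope given arm are both significant, each adjusted for T0 values. Alternatively, report their product with a percentile bootstrap 95% confidence interval, resampling participants within arm.
- Name SICI to MEP amplitude as the pre-specified pair, matching the Hypotheses section, and label other pairs exploratory.
- Remove the statement that the Freedman-Schatzkin test alone identifies mediators at this sample size.

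The cost is a change of wording and a few lines of code on data already being collected, with no extra participants or visits. The downside is fewer mediation claims. At N = 64, with an arm difference of 0.7 SD on the mediator and a correlation of 0.5, power is about 78% by joint significance or bootstrap. The current test shows a nominal 98%, which is not a fair comparator because its error rate is not controlled. With 0.5 SD and a correlation of 0.3, joint significance has about 34% power, so a negative mediation result should be read cautiously.
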